#### Nerve mechanical sensitivity testing

Test of nerve trunk mechanical sensitivity of the brachial plexus, median and ulnar nerves will be performed bilaterally. The ULNT1 (median nerve bias^39^), will be performed as per standard sequence^40^ using 90° abduction and lateral rotation of the shoulder, elbow supination, wrist and finger extension followed by elbow extension. The ULNT3 (ulnar nerve bias^40^) will be performed using shoulder abduction, forearm pronation, wrist and finger extension followed by elbow flexion. The ULNT1 and ULNT3 tests are considered ‘positive’ when there is reproduction of participant’s symptoms and these are changed with the addition of a structural differentiation manoeuvre^39^ (table 1). For the ULNT1, elbow range of flexion at the point of symptom onset will be measured using a digital inclinometer (Trend, DLB Swansea, UK). Mechanosensitivity to pressure will be established by both response to digital pressure and using an algometer (tip size=1 cm^2^, Wagner, USA). The algometer will be used over the ulnar nerve at the proximal cubital tunnel and the carpal tunnel bilaterally. Participants will be asked to inform the researcher at the point where the pressure applied over the nerve changes to pain. Measurements will be taken three times at each site and averages used for analysis. Other sites (bilaterally at brachial plexus in the supraclavicular area, median nerve at the proximal wrist crease, ulnar nerve at Guyon’s canal) will be palpated digitally and graded according to symptom response (see table 1). Phalen’s and Tinel’s test will be performed bilaterally at the wrists.^41^

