### Participant recruitment

Patients aged 18–60 that meet the Quebec Task Force Classification of WAD2 will be recruited within 4 weeks of injury. Participants will be recruited from emergency departments and minor injury units in Surrey, Sussex, Kent and Oxfordshire, directly by clinicians, and following weekly hospital database searches using defined search terms (eg, motor vehicle collision, muscle injury: neck, bruise/contusion/abrasion: neck, sprain/ligament injury: cervical spine). Potential participants will be contacted in person, or by phone, and asked for permission for their details to be passed on to the study team, and/or sent the study details. In addition, posters will be displayed in departments with study contact details. Healthy age-matched and gender-matched control participants will be recruited through departmental emailing lists (Universities of Sussex and Oxford as well as local hospitals), social media and flyers on public notice boards. Potential participants will be screened for suitability via telephone and also be invited to take part in the substudy. Eligible individuals will be sent a participant information sheet and questionnaires to complete (please see table 1 and questionnaire section below) and will be invited to attend a baseline appointment at either Brighton and Sussex Medical School, University of Sussex, Falmer or the Nuffield Department of Clinical Neurosciences, University of Oxford.

**Table 1 T1:** Summary of self-reported and physical assessments

Test	Description	Type of tool/assessment	Participants
Demographics	Age, gender, height/weight.	Self-reported.	HC and whiplash
Injury details	Impact, anticipation.	Self-reported.	Whiplash
Medication details	Specific to WAD symptoms.	Self-reported.	Whiplash
Symptom history	Description of pain or symptoms.	Self-reported.	Whiplash
Pain level	Current pain severity.	Visual Analogue Scale.	Whiplash
Management	Any investigations/treatment.	Self-reported.	Whiplash
Type of pain	Neuropathic pain.	painDETECT Questionnaire.	Whiplash
Disability	Neck disability.	Neck Disability Index.	Whiplash
Psychological factors	Post-traumatic stress. Pain catastrophising. Depression, anxiety and stress. Quality of life.	PTSD-8. Pain Catastrophising Scale. DASS 42. EQ-5D-5L.	Whiplash

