Active range of motion	Cervical spine. Glenohumeral joints. Elbow, wrist and hands.	0–3 scale (0=full range, no symptoms; 1=full range, symptoms; 2=reduced range, no symptoms; 3=reduced range, symptoms).	HC and whiplash
Standardised neurological examination	Sensation (dermatomes C5–T1). Myotomes (C5–T1). Reflexes (biceps, triceps).	Cotton wool (light touch). Neurotip (pinprick). Isometric muscle contraction. Reflex hammer.	HC and whiplash
Bedside sensory testing	Sensation—main pain area and index finger (median nerve/C6 innervation).	Warm/cold coin (thermal) and Neurotip (pinprick).	HC and whiplash
Quantitative sensory testing—index finger	Warm/cold sensation/pain thresholds. Mechanical detection thresholds. Mechanical pain thresholds.	MSA thermal stimulator (Somedic, Stockholm, Sweden). Von Frey filaments (Marstock NerveTest filaments, MRC Systems, Heidelberg, Germany). Weighted pinprick stimulators (MRC Systems, Heidelberg, Germany). Vibration (Tuning fork). Pressure pain threshold (Algometer, Wagner Force dial, Greenwich, USA).	HC and whiplash
Heightened nerve mechanosensitivity	Upper limb neurodynamic test 1 (median nerve bias). Upper limb neurodynamic test 3 (ulnar nerve bias). Nerve palpation. Brachial plexus. Median nerve proximal to carpal tunnel. Ulnar nerve (Guyon’s canal). Ulnar nerve (proximal to cubital tunnel). Median nerve (carpal tunnel). Phalens. Tinels.	Positive/negative test (symptom response changes with structural differentiation). Inclinometer (ROM degrees). Positive/negative test (symptom response changes with structural differentiation). Digital palpation (0–3: 0=no pain or discomfort, 1=local discomfort, 2a=local painful response, 2b=referred pain/symptoms). Algometer and score (0–3). Digital palpation (0–1).	HC and whiplash
MRI	Brachial plexus. Wrist.	T2-weighted images. Diffusion tensor images.	HC and whiplash
Serum samples	Venepuncture.	Inflammatory markers.	HC and whiplash
Skin samples	Skin biopsy.	Density of dermal and intraepidermal nerve fibres using immunohistochemistry.	HC and whiplash

*EQ-5D-5L, Quality of life questionnaire

DASS, Depression, Anxiety and Stress Subscale; HC, healthy controls; PTSD, post-traumatic stress disorder; ROM, range of motion; WAD, whiplash-associated disorder.

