Exclusion criteria include pregnancy, recent history of cervical/arm pain lasting >3 months, previous diagnosis of a peripheral neuropathy, history of systemic illness or autoimmune disease, non-medically controlled hypertension and ongoing steroid treatment. Participants will be assessed for their suitability to undergo MRI. Additionally, healthy control participants must not have had a history of whiplash injury and have not received treatment for neck, thoracic spine or upper limb pain within the past 3 months.

Both recruitment methods and experimental design, in particular length of time of research appointments and MRI scanning, have been discussed and modified based on the comments received from our patient advisory group.

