#### Questionnaires

Patients will complete the following validated questionnaires: Neck Disability Index (NDI),^31 32^ pain detect questionnaire (painDETECT),^33^ short post-traumatic stress inventory (PTSD-8),^34^ Pain Catastrophising Scale (PCS),^35^ Depression, Anxiety and Stress Scale (DASS42),^36^ the quality of life questionnaire (EQ-5D-5L),^37^ and the Impact of Events Scale (IES-Revised).^38^

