### Statistical analysis

Data will be exported to Stata (V.17, StataCorp, Texas, USA) for analysis. The distribution of the data will be checked for normality, and parametric, or non-parametric methods will be used as appropriate. Participants’ characteristics will be described at all time points.

For objective 1, regression analysis, or non-parametric tests, will be used as appropriate to identify differences in MRI parameters (T2-weighted STIR 4 nerve roots per side, nerve morphology and DTI parameters) and clinical tests (eg, neuropathic pain scores, tests of nerve mechanosensitivity, QST and serum inflammatory markers) between participants with acute WAD2 and age/gender-matched controls. Regression analysis will be used to assess associations with age and height.

For objective 2, recovery of participants with WAD2 will be determined at 6 months with the Neck Disability Index and a global recovery question. The analysis will be conducted with three models using different predictors measured in the acute stage: (a) MRI parameters of neuroinflammation, (b) clinical parameters that reflect neuroinflammation and (c) the addition of MRI to clinical parameters to determine whether this improves predictive strength. The dependence between MRI and clinical assessments will be investigated and composite measures added to the model. In addition, a linear regression will be performed of Neck Disability Index scores on measures of neuroinflammation.

For objective 3, mixed effects modelling will be used to compare MRI and clinical measures between recovered and non-recovered participants with WAD2 over time.

For objective 4, multivariable regression will be used to investigate the relationship of each MRI variable with the clinical parameters of neuroinflammation. In addition, a regression analysis will be performed between clinical measures of neuroinflammation and MRI parameters.

For the substudy, independent t-tests or non-parametric alternatives will be used to compare dermal and intraepidermal nerve fibre density in skin biopsies in patients in the acute phase after whiplash injury with healthy controls. Separate regression models will be used to investigate whether changes in nerve fibre density in the acute stage predict pain persistence at 6 months.

Data reduction techniques (eg, principal components analysis) may be used prior to regression modelling.

Missing data will be managed with multiple imputation strategies.

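### Two objective 1 patient-control comparisons are not valid as written: binary ULNT positivity, which the text ties to the participant's own symptoms, and neuropathic pain scores, which only patients are given

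*Protocol article*

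**What the plan says.** All references are to the protocol article.

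- **Statistical analysis, objective 1.** MRI parameters are compared between groups, and so are "clinical tests (eg, neuropathic pain scores, tests of nerve mechanosensitivity, QST and serum inflammatory markers) between participants with acute WAD2 and age/gender-matched controls".
- **Nerve mechanical sensitivity testing.** A ULNT1 or ULNT3 result counts as positive only "when there is reproduction of participant’s symptoms and these are changed with the addition of a structural differentiation manoeuvre". The sentence ends by pointing to Table 1. For ULNT1 only, the elbow angle at which symptoms begin is also measured with an inclinometer.
- **Table 1, nerve mechanosensitivity row.** The row is marked for healthy controls and whiplash participants. Its rule is "Positive/negative test (symptom response changes with structural differentiation", with no requirement that the participant's own symptoms be reproduced.
- **Participant recruitment, exclusion criteria.** Beyond the general exclusions, "healthy control participants must not have had a history of whiplash injury and have not received treatment for neck, thoracic spine or upper limb pain". The bar on treatment looks back 3 months.
- **Table 1, type of pain row.** The tool is the "painDETECT Questionnaire", assigned to whiplash participants only. The Questionnaires section agrees: "Patients will complete the following validated questionnaires", and painDETECT is on that list.
- **Abstract.** One sentence covers the recruitment of both groups and the completion of questionnaires, so it can be read as including controls.

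**The concern.** A between-group comparison needs an outcome that both groups can have. Two of the comparisons named for objective 1 fall short of this.

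For the binary ULNT result, the rule in the text sets a condition that patients can meet and healthy controls mostly cannot. A control whose arm response is evoked by the test and changes with structural differentiation would still be scored negative, for lack of a presenting complaint. A higher positive rate in patients would then partly reflect that patients have symptoms and controls do not. The article counts it as a strength that the study may show whether simple clinical tests identify nerve inflammation, so readers are likely to take this contrast as evidence of nerve pathology. With two wordings in force, two sites and examiners who know the participant's group, the same control could also be scored differently.

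For neuropathic pain scores the problem is simpler. If controls are not given painDETECT, there is nothing to compare, and no analysis plan can supply the missing data.

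**Working it through.** **The plan's own figure.** The only objective 1 sample size rests on MRI signal: SD 0.1, ICC 0.45, 8 assessments per participant, difference 0.06, ratio 3:1, 80% power, 5% significance (taken as two-sided).

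- Variance of a participant's mean: 0.1² × (1 + 7 × 0.45)/8 = 0.0051875, so SD = 0.0720.
- Controls: (1.960 + 0.842)² × 0.0051875 × (1 + 1/3)/0.06² = 15.1, rounded up to 16, with 48 whiplash participants.

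This matches the stated 48 and 16. It does not involve the clinical tests, so the present point leaves it untouched.

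**ULNT: how far a restricted control group carries the result.** The inputs are 115 patients and 34 controls (Sample size calculation). The article gives no positivity rates, so the check asks how many positive patients give two-sided p < 0.05 in Fisher's exact test when the control count is held at a low value. Fisher's test is chosen here for illustration. The article says only regression or non-parametric tests as appropriate.

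Worked case, 13 positive patients and 0 positive controls:

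- Probability that none of 13 positives is a control: C(115,13)/C(149,13) = 0.0292.
- Opposite-tail tables that are no more probable (7 or more of the 13 being controls): 0.0110.
- Two-sided p = 0.0292 + 0.0110 = 0.040.

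| Positive controls | Smallest positive patient count with p < 0.05 | p | p with one patient fewer |
|---|---|---|---|
| 0/34 | 13/115 (11.3%) | 0.040 | 0.069 |
| 1/34 | 19/115 (16.5%) | 0.046 | 0.075 |
| 2/34 | 24/115 (20.9%) | 0.043 | 0.067 |

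With 0/34, p falls below 0.01 at 19/115 (p = 0.007). With the 96 patients and 32 controls that the article requires for objective 1, and 0/32 positive, the threshold is 12/96 (p = 0.037).

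If controls are held at 0/34, the chance of p < 0.05 is 36% at an assumed true patient positive rate of 10%, 99.5% at 20% and close to 100% at 30%. In an ordinary logistic model, 0/34 would also leave an empty cell and no finite estimate of the group effect.

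**painDETECT: the passages side by side.**

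| Place | Who has a neuropathic pain score |
|---|---|
| Statistical analysis, objective 1 | Implied for both groups (compared between them) |
| Table 1 | Whiplash only |
| Questionnaires | Patients only |
| Abstract | Can be read as both groups |

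Other Table 1 rows are marked for both groups, so the restriction looks deliberate. On Table 1 and the Questionnaires section, the comparison has no control data.

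**The case against.** The strongest reply is that the text rule should be read together with Table 1, to which it refers. Table 1 lists the tests for both groups in wording that controls can meet. The same section also speaks of symptom onset and symptom response for everyone tested, so symptoms might mean any evoked response. This is a fair reading and it stands in part: it shows that the article can be reconciled. It does not show that the stricter sentence is harmless, because that sentence is the explicit definition of a positive test and refers to the participant's symptoms.

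A reader might infer that controls score zero by definition, so that a significant result says nothing about nerves. The documents do not support that. Eligibility excludes whiplash history, recent neck or arm pain lasting more than 3 months and recent treatment, but not every minor untreated symptom. A patient must also show a change with structural differentiation, so the patient rate still carries information. The defect is unequal opportunity to score positive, and the table above shows that the threshold moves with one or two positive controls.

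A reader might also infer that the clinical comparisons fail as a whole, or that the painDETECT comparison certainly cannot be run. Neither follows. ULNT1 range, algometer thresholds, graded palpation, QST and serum markers can all be scored in controls. The article does not say that the binary ULNT result is the mechanosensitivity variable to be compared, and that choice may be made in an analysis plan not shown. The abstract leaves open that controls complete the questionnaires, and the objective 1 list is given as examples.

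**Conclusion.** The point holds in limited form. Followed as written, the binary ULNT1/ULNT3 contrast between patients and controls is biased towards a difference, and the neuropathic pain comparison lacks control data unless the abstract, rather than Table 1 and the Questionnaires section, describes what is done. The ULNT part assumes that the text rule is applied literally to controls and that they seldom have symptoms to reproduce. On that basis about 11% positive patients is enough for p < 0.05 with no positive control, rising to about 17% with one and 21% with two. These are thresholds, not predictions. The Introduction does report that such tests provoke symptoms in many patients, so passing them is plausible.

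The MRI comparison on which objective 1 is built, its sample size and the remaining clinical measures are unaffected, as are the patient-only analyses of objectives 2 to 4. The point merits correction because the article contradicts itself, which is more than detail left to an analysis plan.

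**What to change.** 1. Reconcile the ULNT rule in the nerve mechanical sensitivity section with Table 1. For objective 1, use one criterion that both groups can meet: an evoked response that changes with structural differentiation, as Table 1 has it, where this was recorded.
2. Make ULNT1 elbow range at symptom onset the preferred between-group measure. It is already collected.
3. If only the own-symptoms version of ULNT3 was recorded, do not interpret ULNT3 positivity between groups. ULNT3 has no range measure to fall back on.
4. Keep own-symptoms positivity for the patient-only analyses.
5. Reconcile the abstract, Table 1, the Questionnaires section and the objective 1 analysis on who completes painDETECT. Remove neuropathic pain scores from the objective 1 comparison unless controls do complete it.

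The cost is mostly wording. The possible exception is carrying two ULNT codings, one for the group comparison and one for the patient-only analyses. Recruitment began in July 2021 and the article does not show that both were recorded, so the existing records need checking first.

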#### Quantitative sensory testing

QST will be carried out over the ventral aspect of the proximal phalanx of the index finger and the thenar eminence according to the German Network for Neuropathic Pain protocol.^42^ Additionally, we will perform warm detection, cold detection and pressure pain thresholds over the contralateral lower limb (upper anterolateral aspect of the tibia) to assess for any systemic changes to QST. Thermal detection and pain thresholds (heat and cold) will be measured using a Thermotester (Somedic, Sweden) and mechanical detection and pain thresholds with von Frey filaments (Optihair 2 MRC Systems, Germany), Rydel Seiffer tuning fork, an algometer (Wagner, USA) and weighted pinprick stimulators (MRC Systems, Germany). QST will be carried out on the most symptomatic side in WAD2 participants and non-dominant side in healthy control participants.

#### MRI)

Images of the brachial plexus and median nerve at the wrist (on the most symptomatic side in patients and dominant side in healthy control participants) will be obtained at each research site using a 3-Tesla scanner of the same manufacturer and model (Siemens Prisma, Siemens Medical Solutions, Erlangen, Germany) with a dedicated 64 channel head/neck coil and a small 4-channel flex coil for the wrist.

For brachial plexus imaging, participants will be positioned supine. Coronal images will be obtained using a two-dimensional multislice T1-weighted (slice thickness=3 mm) and a T2-weighted short tau inversion recovery (STIR) three-dimensional (3D) SPACE sequence (slice thickness=0.8 mm). For the wrist, participants will be positioned with their arm above their head in a reverse superman position with the wrist in the centre of the bore using a flex coil. Axial images will be obtained using a T1-weighted (slice thickness=3.0 mm) and a T2-weighted STIR sequence with flow suppression (slice thickness=1.5 mm). A 3D balanced steady-state free precession (bSSFP) will also be acquired as anatomical reference. The sequence will be repeated twice, with phase cycling, to minimise banding artefacts.^26^

DTI will also be obtained. For the brachial plexus, we will use Readout Segmentation Of Long Variable Echo trains (RESOLVE) sequences,^43^ which provide data with low distortions and clinically feasible scan times. For the wrist, we will use diffusion-weighted echo-planar imaging. This acquisition was preferred for the wrist because it provides higher signal-to-noise than RESOLVE.^26^ DTI images will be registered to structural images using T1-weighted images for the neck and bSSFP for the wrist.

In the unlikely event of a structural abnormality being noted incidentally, a radiologist or neurologist would be asked to review the scan and, if there remained any concerns, the patient would be contacted through their general practitioner or directly by the neurologist to arrange a formal diagnostic scan.

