### Study design

This is a prospective cohort study at two centres. A total of 115 participants will be recruited following a whiplash injury within 1 month of their original injury. We will also recruit 34 healthy proportionally age-matched and gender-matched control participants. People with acute WAD2 and healthy control participants will attend a baseline appointment. In addition to MRI, a detailed musculoskeletal assessment will be performed, as well as tests of nerve trunk mechanical sensitivity and quantitative sensory testing (QST). A blood sample will be taken and analysed for levels of inflammatory markers. Participants will also be asked to complete a series of validated questionnaires to assess neuropathic symptoms, functional deficits, quality of life and psychological factors. For the substudy, skin biopsies from the index finger and ankle will also be taken. At 6 months, the Neck Disability Index and a self-rated global recovery question will be used to determine recovery. A sequential sample of patients will be invited to attend a follow-up appointment during which the same detailed assessments will be repeated (figure 1).

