### Sample size calculation

Mean nerve signal intensity ratio data from our previous cross-sectional study of 13 controls and 9 participants with chronic WAD2 were analysed using a linear mixed model.^9^ The observed difference in means between controls and WAD2 participants was 0.0600 (SE=0.0315) for the C5–C8 roots of the brachial plexus, which was statistically significant; age was not a statistically significant covariate. The intraclass correlation coefficient of the nerve signal ratio was estimated to be 0.45. Assuming that there are eight assessments per participant (two sides × four roots), a SD of 0.1, intraclass correlation coefficient of 0.45 and a ratio of 3 participants with whiplash to one healthy control, the study would require 48 participants with whiplash and 16 controls to detect an effect estimate of 0.06 for the mean nerve signal intensity difference (80% power, 5% significance). Since in the acute stage it is estimated that only 50% of the participants with whiplash will develop chronicity,^51^ we will need to image 96 participants with whiplash and 32 controls for objective 1 (difference in neuroinflammation in the acute stage). Based on ~48 participants who have not recovered at 6 months, we would be able to fit a logistic regression model with 5–10 predictor variables for objective 2 (predictive factors of chronicity).

For objective 3 (development of neuroinflammation over time), we will ask 25 participants who have recovered and 25 participants who have not recovered to return at 6 months, which will enable an effect size of 0.9 to be detected using analysis of covariance, with 95% power for 5% significance. This value assumes that the correlation between the acute and chronic measurements is 0.5.

For objective 4 (validity of low cost tests of neuroinflammation), with nine independent variables, a rule of thumb for a multiple linear regression (ie, 10 participants per additional variable) implies that data from 90 participants with whiplash should be adequate to explore this.^52^

For the substudy, 68 participants with whiplash and 34 healthy controls (80% power, 5% significance, 0.53 effect size, one-tailed test) would allow the detection of a 20% smaller difference in intraepidermal nerve fibre density in the acute stage compared with healthy controls based on our previous cohort of patients with chronic WAD2.^53^

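### Healthy controls have wrist MRI on the dominant side but QST on the non-dominant side, so at least one patient-control comparison is unbalanced for hand dominance

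*Protocol article*

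**What the plan says.** Two subsections of the protocol article's *Baseline and follow-up appointment* section fix the side for unilateral measures.

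- *MRI*: the median nerve at the wrist is imaged "on the most symptomatic side in patients and dominant side in healthy control participants".
- *Quantitative sensory testing*: "QST will be carried out on the most symptomatic side in WAD2 participants and non-dominant side in healthy control participants".

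The patient rule is therefore the same for both measures, and the control rule is reversed between them. Neither subsection explains the difference.

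Both measures feed objective 1. *Statistical analysis* compares MRI parameters and clinical tests, the latter including "tests of nerve mechanosensitivity, QST and serum inflammatory markers) between participants with acute WAD2 and age/gender-matched controls". Matching is described under *Study design*: "We will also recruit 34 healthy proportionally age-matched and gender-matched control participants". On covariates, *Statistical analysis* adds: "Regression analysis will be used to assess associations with age and height". The adjustment under *Standardisation across the two sites* deals with site. None of these statements concerns which limb was tested.

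**The concern.** In a patient-control comparison of a one-sided measure, the two groups should be alike in everything about the limb except the injury. Here they are not. Patients contribute some mix of dominant and non-dominant limbs, because symptoms decide the side. Controls contribute only dominant limbs for wrist MRI and only non-dominant limbs for QST. If a measure differs between a person's dominant and non-dominant hand, part of that difference is carried into the patient-control contrast, where it could mimic or hide an effect of injury.

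The two measures also address related tissue: the median nerve at the wrist, and skin of the index finger and thenar eminence (Table 1 links the index finger to median nerve/C6 innervation). In patients they come from the same limb; in controls they come from opposite limbs. If wrist MRI and QST disagreed about a group difference, the side rule would be one possible explanation.

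**Working it through.** **The plan's own figure.** The objective 1 sample size rests on "Assuming that there are eight assessments per participant (two sides × four roots), a SD of 0.1", with "intraclass correlation coefficient of 0.45 and a ratio of 3 participants with whiplash to one healthy control". The effective SD of a participant mean is 0.1 × √[(1 + 7 × 0.45)/8] = 0.1 × √0.51875 = 0.0720. To detect 0.06 with 80% power at two-sided 5% (two-sided is assumed here), controls needed = (1 + 1/3) × (1.960 + 0.842)² × 0.0720²/0.06² ≈ 15.1, so 16, with 48 whiplash participants. This reproduces the stated 48 and 16, which the plan doubles to 96 and 32. The calculation uses roots on both sides, so the side rule does not touch it.

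**Inputs for the side question.**
- Share of controls measured on the dominant limb: 1 for wrist MRI, 0 for QST (from the two subsections).
- Share of patients measured on the dominant limb: p. Not given; assumed between 0.3 and 0.9.
- Dominant minus non-dominant difference in a measure: d, in SD units. Not given; shown at 0.2 and 0.5. It may differ in size and sign from one measure to another.
- Group sizes: 96 patients and 32 controls.

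**Imbalance (patients minus controls).** Wrist MRI: p − 1. QST: p − 0 = p. For p between 0 and 1 the absolute values add to (1 − p) + p = 1, so reducing one increases the other by the same amount.

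**Bias** = d × imbalance, in SD units.

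**Type I error** of an unadjusted two-sided 5% test, by normal approximation. The standard error is √[(1 + p(1 − p)d²)/96 + 1/32]; without the small mixing term it is √(1/96 + 1/32) = 0.204. At p = 0.5 and d = 0.5 it is √(1.0625/96 + 1/32) = 0.206, so bias/SE = 0.25/0.206 = 1.22, and the rejection probability is Φ(−1.96 − 1.22) + 1 − Φ(1.96 − 1.22) ≈ 0.229.

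The table takes d as positive for both measures, purely for display. Each cell gives the bias in SD, then the type I error.

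| p | Imbalance MRI / QST | d = 0.2, MRI | d = 0.2, QST | d = 0.5, MRI | d = 0.5, QST |
|---|---|---|---|---|---|
| 0.3 | −0.7 / +0.3 | −0.14, 10.5% | +0.06, 6.0% | −0.35, 39.9% | +0.15, 11.3% |
| 0.5 | −0.5 / +0.5 | −0.10, 7.8% | +0.10, 7.8% | −0.25, 22.9% | +0.25, 22.9% |
| 0.7 | −0.3 / +0.7 | −0.06, 6.0% | +0.14, 10.5% | −0.15, 11.3% | +0.35, 39.9% |
| 0.9 | −0.1 / +0.9 | −0.02, 5.1% | +0.18, 14.3% | −0.05, 5.7% | +0.45, 59.4% |

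With d = 0, every bias is 0 and every error rate is 5%.

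**Reach.** *Sample size calculation* counts roots on two sides and *Statistical analysis* refers to roots per side, so the side rule is read here as governing the wrist and not the brachial plexus. *Nerve mechanical sensitivity testing* is bilateral. Objectives 2 and 3 compare patients with patients. Objective 4 is sized on whiplash participants, so the opposite limbs in controls would matter there only if controls were included.

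**The case against.** The strongest reply has four parts.

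1. **The two rules are not a strict contradiction.** They govern different procedures and both can be followed as written. One may also be a slip of wording, in which case controls would have one rule. That is fair. But the text as it stands gives two rules and no reason, and even a single rule, all dominant or all non-dominant, would leave both measures unbalanced against a mixed patient group.

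2. **Imbalance is not bias.** No section says that median nerve T2 signal, a diffusion parameter or any sensory threshold depends on hand dominance. This stands in full: the documents establish the imbalance, while the size of any bias rests on assumed values.

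3. **The direction of bias is not fixed.** A reader might infer that MRI and QST results are biased in opposite directions. The documents do not support that. Only the imbalances have opposite signs. Each bias also takes the sign of its own d, and there are several MRI and several QST measures; if d differs in sign between two of them, their biases point the same way.

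4. **An article may leave covariates to a fuller document.** This also stands: the lack of a named side covariate is not the point. The point is the side rule, which is stated. An analysis covariate could repair it only in part, because under the present rule no control varies in side for a given measure.

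**Conclusion.** The point holds as an unexplained inconsistency in the control side rule, with a certain imbalance and an unknown bias. For any p, at least one of wrist MRI and upper-limb QST is unbalanced for dominance in the patient-control comparison, and for every p strictly between 0 and 1 both are. At p = 0.5, an assumed dominance effect of 0.2 to 0.5 SD would give a bias of 0.10 to 0.25 SD in absolute size and a type I error of about 8% to 23% in place of 5%. These figures are illustrations resting on assumed p and d, a common standardised scale and an unadjusted comparison; they are not estimates for this study.

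A reader might go further and infer that the study's main imaging result or its sample size is compromised. It is not: the endpoint used for sizing is bilateral, and the prognostic and longitudinal objectives involve patients only. What is exposed is a subset of the objective 1 comparisons.

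**What to change.** Reconcile the *MRI* and *Quantitative sensory testing* subsections to one control rule. In each remaining control, do wrist MRI and QST on the same limb, and allocate that limb so that the dominant/non-dominant proportion matches the limbs tested in patients. If all controls followed this rule, the imbalance would be zero whatever d is, and the sample size would not change.

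Recruitment began in July 2021, so some controls may already have been tested. If a fraction f of controls followed the present rules and the rest are allocated at p, the control share of dominant limbs is f + (1 − f)p for MRI and (1 − f)p for QST. The remaining imbalance is then f(p − 1) and fp: reduced in proportion, not removed.

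Therefore also record handedness and limb tested for every participant, and report a sensitivity analysis of the wrist MRI and QST comparisons that adjusts for whether the dominant limb was tested. State its limits: the coefficient comes mainly from patients, whose side is chosen by symptoms, so it may mix dominance with symptom laterality, and it assumes no interaction with group.

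The cost is one line of procedure, two recorded items and one extra covariate, with no added scan or test. The downside is two side rules within the 34 controls, which should be reported.
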